**Figure 2 f2:**
[figure not shown]
Schedule of enrolment, study questionnaires, and tasks.

### Adherence and monitoring

Adherence to the sleep schedule and task completion is monitored throughout participation.

#### Sleep schedule adherence

The sleep schedule is set in collaboration with the participant based on self-reported habitual sleep schedule. Each night and morning of the study, participants call the study phone and leave a message to indicate sleep and wake times. Sleep diaries and participant phone calls are monitored daily by the researchers. Within the first three nights of participation, if it is clear that the participant’s sleep schedule is different than what was initially set, the sleep schedule is adjusted to match the participant’s actual sleep schedule, as long as it stills falls within the study criteria (they do not sleep before 22:00 or after 01:00 and do not wake before 06:00 or after 09:00). If the sleep schedule is adjusted, participant wake time on the day of the lab session is also adjusted (to 2 h prior to regular wake time), as is lab session timing. Based on sleep diaries and sleep/wake time phone calls, participants are excluded from the study if they do not adhere to the sleep schedule for at least five nights. Non-adherence includes napping, going to sleep too early, or oversleeping. Participants are also excluded from the study if they wake 30 min after their scheduled wake time on the day of the lab session. If a participant is non-adherent to the sleep schedule, participation is rescheduled if there is agreement that they will be able to adhere for the rescheduled week. After the lab session, the sleep schedule is followed for one more evening. If participants are non-adherent to the sleep schedule on this evening (eg, napping following the lab session), they are excluded from the study and cannot be rescheduled.

#### Trauma films and intrusive memory diary adherence

Participants must be observed to be looking at the screen at least 80 per cent of the time when watching the films or to have rated their level of attention to the most graphic parts of the film as at least 5, on a 1 (*none at all*) to 9 (*total attention*) point scale. Participants are asked to complete the intrusive memory diary online each day and are contacted the following day via email if they have not completed it.

#### Mind wandering task adherence

Participants are contacted during the study if they do not complete tasks or are non-adherent. Participants who do not complete the mind wandering task between the hours of 14:00 and 17:00 are contacted by researchers on the day via email and asked to complete the task as soon as possible. If the participant cannot complete the task prior to 12 h after their wake time for that day (based on the sleep diary and phone call), they are asked not to complete the mind wandering task for that day.

## Analytic strategies

All analyses will be conducted in R.

Aim 1: The effect of a daytime nap (vs wake) on total intrusive memory frequency will be analyzed with a generalized linear mixed-effects model. Sex and day will be included as covariates. A random intercept for participant will be included to account for repeated measures across days.

Aim 2: The effect of sleep-related memory consolidation on intrusive memory frequency will be analyzed with regression and mediation analysis. Specifically, Hypothesis 2a (a nap will lead to greater recognition memory for the trauma film) will be examined with multiple regression, whereby recognition memory immediately after the nap/wake will be predicted by Condition. For Hypothesis 2b (recognition memory will mediate the relationship between sleep and intrusive memories), we will utilize mediation analysis, with Condition as the explanatory variable, recognition memory immediately after the nap/wake as the mediator, and total number of reported intrusive memories as the dependent variable. A Monte Carlo power analysis was conducted for the mediation model. A sample size of *n* = 114 has limited power to detect the indirect effect. Nonetheless, given the strong theoretical rationale for the mediation analysis and the value for future research in determining effect sizes, we will conduct the analysis and consider Hypothesis 2b as a secondary analysis. We will report effect sizes and confidence intervals of each path. We will also conduct parallel exploratory analyses for both Hypotheses 2a and 2b, utilizing recognition memory on day 5, rather than memory immediately following the nap/wake. This will explore the role of longer-delay memory consolidation on intrusive memory. Note, Hypothesis 2b may appear dependent on the success of Aim 1.

Aim 3: The effect of overnight sleep on next-day mind wandering and intrusive memory frequency will be analyzed with mixed models. In two separate analyses, Hypothesis 3a (reduced sleep will be associated with increased mind wandering and increased intrusive memories the next day) will use sleep (total sleep time, sleep efficiency) each night to predict frequency of mind wandering and number of intrusions the next day. Hypothesis 3b (mind wandering will mediate the relationship between sleep and intrusive memories the next day) will be tested with two mediation analyses. Sleep duration each night will serve as the explanatory variable, mind wandering the next day will serve as the mediator, and number of intrusions the next day will be the dependent variable. Hypothesis 3b is also considered a secondary analysis. We were unable to perform a power analysis for this mediation as there are no previous studies examining the effect of sleep on both spontaneous cognition and intrusive memories, and thus, no basis for estimating effects sizes. If this mediation model is significant, as an exploratory analysis, we will also run a moderated mediation to explore if Condition moderates the relationship between mind wandering and intrusive memories, in the context of the mediation analysis. A separate set of models with sleep efficiency as the explanatory variable will also be run as an exploratory analysis. If the structure of the data (eg, excessive zero counts in the intrusive memory data) does not allow for mediation, alternative analytical strategies will be developed to address the same aim for Hypotheses 2b and 3b.

For Hypothesis 1 and Hypothesis 3a, we will run additional secondary analyses to examine the influence of trait mind wandering, mindful attention, frequency of intrusive thoughts, perseverative thinking and maladaptive daydreaming on the relationship between sleep and intrusive memories. Each trait measure will be examined in a separate model, where the given trait measure is added to the primary model for Hypotheses 1 or 3a. We will examine the main effect of the trait measure, as well as the interaction between the trait measures and the primary effect of interest for each model. These analyses will allow us to determine if trait factors theoretically related to the vulnerability to intrusive memory or mind wandering influence the sleep effect.

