### Participants and recruitment

#### Sample size

Our target sample size is 114 participants, with 57 in each condition. This study is powered primarily on Hypothesis 1, the group effect (nap vs. wake) on intrusive memory frequency. Relevant effect sizes were derived from a variety of prior studies, which have also been reported within at least one of four meta-analyses. Previous studies [14, 15, 25] examining the effect of a nap compared to wake on intrusion frequency have detected small to medium effect sizes (Hedges’ *g* = 0.38 [26] and 0.69 [15]) for between-group differences in intrusive memory frequency in the days following the experimental manipulation. Gvozdanovic et al. (2023) [14] also found a nap led to significantly fewer intrusive memories than the wake group, however, an effect size was not provided. For studies examining recognition memory for the trauma film following overnight sleep compared to wake or partial sleep deprivation [13, 23, 40], we calculated a sample size weighted average for Cohen’s *d*, finding a medium effect size of 0.5 for between-group differences where sleep, relative to wake, led to improved recognition memory for the film. Consistent with these studies, to detect a medium effect size of 0.5, with a two-tailed α of 0.05 and 80 per cent power, 57 participants are needed per group (114 participants in total) [41].

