#### Randomization

During the lab session (day 0), participants are randomly assigned to one of the two groups: an experimental (nap) group and a control (wake) group. All participants are mildly sleep deprived the morning of the lab session to increase the probability individuals in the nap group can both sleep and experience REM sleep. Participants are blinded to group allocation until immediately prior to the nap/wake period. Researchers are blinded to participant group allocation until after polysomnography set-up is complete. Thus, the polysomnography set-up for the wake group serves as a sham and to allow verification of sustained wakefulness during the experimental period. Groups of six participants are block randomized in equal numbers to each group and film order (out of two films), stratified by sex, to increase the likelihood of equal assignment over time. A researcher not involved in the administration of lab sessions ([name]) created a spreadsheet of participant allocation to group and film order using https://www.sealedenvelope.com/simple-randomiser/v1/lists. Cell blackout is used to conceal allocation until the researcher responsible for project administration ([name]) has completed polysomnography set-up.

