##### Trauma film paradigm

The trauma film paradigm is used in this study to elicit intrusive memories [17]. Clips from two films are viewed in a small, sound attenuated room, and presented on a 24-inch screen with over-ear headphones for audio. Participants first complete a questionnaire about their current emotional state. They watch the trauma film (~12 min in total), which includes two scenes, one from the film Irréversible [57] and the other from a UK public safety advertisement on the dangers of texting and driving [58]. Both film scenes are fictional and have been used in previous studies [56, 59–63]. Film order is counter-balanced. Whilst participants view the films, we ask they maintain their concentration and continuously look at the scene. Upon completion, they rate their current level of distress and degree to which they were able to pay attention to the films. A camera in the room is used to monitor participants’ attention to the film. Participants are told prior to participating in the study they may watch positive, neutral or negative scenes, and are informed about the contents of the negative scenes prior to watching.

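### Hypothesis 2b names no covariates, so its recognition-to-intrusions path is unprotected against confounding by film encoding; for Hypotheses 1 and 2a the same omissions cost only precision

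*Protocol article*

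**What the plan says.** All places are in the protocol article.

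- **Allocation (Randomization).** "Groups of six participants are block randomized in equal numbers to each group and film order (out of two films), stratified by sex". Sex is therefore a stratifier, and film order is allocated together with group.
- **Ratings (Trauma film paradigm).** "Upon completion, they rate their current level of distress and degree to which they were able to pay attention to the films". Under Study design, this comes before the nap or wake period. Under Randomization, participants do not know their group until just before that period starts.
- **Hypothesis 1 (Analytic strategies).** "Sex and day will be included as covariates", with a random intercept for participant. Film order and the ratings are not named.
- **Hypothesis 2a.** Described as multiple regression in which "recognition memory immediately after the nap/wake will be predicted by Condition". No other predictor is named.
- **Hypothesis 2b.** A mediation analysis "with Condition as the explanatory variable, recognition memory immediately after the nap/wake as the mediator" and total intrusions as the outcome. No covariate is named. It is declared secondary, with limited power, and is kept partly to supply effect sizes for later research; each path is to be reported with a confidence interval.
- **Stated uses of the ratings.** Attention serves an exclusion rule (Data exclusion). Distress serves an optional exploratory subgroup (Subgroup analysis).
- **Other baseline variables.** Five trait measures are added one at a time in secondary models for Hypotheses 1 and 3a, not for 2a or 2b.

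**The concern.** In Hypothesis 2b only Condition is randomised. That protects the effect of Condition on recognition and its effect on intrusions. It does not protect the effect of recognition on intrusions (the b path), because recognition is observed, not assigned.

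How closely a participant watched the film, and how strongly they reacted, could plausibly affect both how well it is remembered and how often it intrudes. The consolidation account needs a negative b path: better recognition, fewer intrusions. A common cause that raises both pushes the estimate upwards and could hide that path. The article states neither a no-confounding assumption nor a sensitivity analysis for this path.

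Secondary status and low power do not remove the problem. Low power widens the interval; confounding moves the estimate, and the path estimates are what the article says it will report.

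For Hypotheses 1 and 2a less is at stake. Leaving out allocation factors and pre-manipulation predictors gives away some precision in a randomised comparison that stays unbiased.

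**Working it through.** **1. The plan's own power figure, needed as a baseline.** The Sample size section states that "This study is powered primarily on Hypothesis 1, the group effect (nap vs. wake) on intrusive memory frequency" and sets the size "to detect a medium effect size of 0.5, with a two-tailed α of 0.05 and 80 per cent power", giving 57 per group.
- n per group = 2(1.960 + 0.842)² / 0.5² = 62.8, so 63 (normal approximation), or 64 by the exact t calculation. The stated 57 is not reproduced.
- At 57 per group the exact t power is 75.4% (normal approximation 76.1%).

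The mismatch is a separate matter. Here 75.4% is only the reference for the gain from adjustment.

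**2. Bias in the b path of Hypothesis 2b.** The documents give no correlation of distress or attention with recognition or intrusions, so these values are assumed. Let a pre-manipulation factor U have correlation r with recognition within condition and a direct standardised effect of the same size r on intrusions. When the true b is zero, that direct effect equals U's correlation with intrusions within condition. Omitting U then biases b by about r × r:
- r = 0.2: 0.2 × 0.2 = +0.04
- r = 0.3: 0.3 × 0.3 = +0.09
- r = 0.4: 0.4 × 0.4 = +0.16

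Against an assumed true path of -0.2 to -0.3, the smallest share is 0.04/0.3 = 13% and the largest is 0.16/0.2 = 80%. If U acted on recognition and intrusions in opposite directions, the product, and so the bias, would be negative.

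**3. Simulation check.** Linear mediation, 114 participants, Condition-to-recognition effect 0.5 SD, 4,000 runs:

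| r | true b = 0: mean unadjusted b | true b = 0: rejection at nominal 5% | true b = -0.2: mean unadjusted b | true b = -0.2: rejection |
|---|---|---|---|---|
| 0.2 | +0.04 | 8% | -0.16 | 41% |
| 0.3 | +0.09 | 15% | -0.11 | 21% |
| 0.4 | +0.16 | 40% | -0.04 | 7% |

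With U in the model, bias is about 0, rejection under true b = 0 is 4-5%, and power at b = -0.2 is about 55%.

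**4. Precision in Hypotheses 1 and 2a.** Linear two-group approximation: a covariate with correlation r to the outcome has R² = r², and the standardised effect becomes 0.5/√(1 - R²). Exact t power at 57 per group:
- r = 0.2 (R² = 0.04): 77.1%
- r = 0.3 (R² = 0.09): 79.2%
- r = 0.4 (R² = 0.16): 82.3%

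At R² = 0.02 power is 76.2%, under one point above 75.4%.

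Hypothesis 1 uses a generalised linear mixed model, so a rough count-scale check was also run. It used Poisson totals with robust standard errors, 800 runs, and assumed a mean of 4, a between-person SD of 0.8 on the log scale and a rate ratio of 0.65. A covariate explaining 10%, 20% or 30% of between-person variance raised power by about 2, 6 or 8 points.

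**5. Omitting a balanced allocation factor.** This does not bias the group contrast. It makes the test slightly conservative: true alpha = 2[1 - Φ(1.96/√(1 - R²))], which is 0.048 at R² = 0.02 and 0.044 at R² = 0.05.

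**The case against.** - **Hypothesis 1 already adjusts for sex, the only stratifier.** Correct. Among allocation factors it lacks only film order, and nothing in the article shows that order predicts intrusions.
- **Adjustment in a randomised comparison is optional, and the correlations are assumed.** Also correct. A reader might infer that Hypotheses 1 and 2a are biased. The documents do not support that: the cost is a modest amount of precision and could be negligible.
- **Blocks of six.** Six cannot be divided equally over four group-by-order cells (6/4 = 1.5), and a reader might infer that film order is unbalanced between groups. But the sentence can mean balance on each factor separately, and three and three by group with three and three by order is feasible. The point is peripheral.
- **The article is condensed.** Calling Hypothesis 2a multiple regression while naming one predictor suggests unlisted covariates, and the preregistration, not available here, may name them. This lowers confidence about 2a. The article does name covariates for Hypothesis 1 and gives the ratings other specific uses, so the models are still fairly judged as written.
- **Hypothesis 2b is secondary, and both the size and the sign of any confounding are assumed.** This stands as a limit on the claim. The attention exclusion may also narrow the range of that rating and so its influence. It does not give the path any protection.

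**Conclusion.** The point holds in a limited form. As written, Hypothesis 2b leaves the recognition-to-intrusions path unprotected against confounding by encoding strength, although two relevant ratings are collected before the manipulation. A reader might infer that the path is confounded as a matter of fact. The documents do not show that; it is an uncontrolled risk of unknown size. Under assumed relations of 0.2 to 0.4 in the same direction with recognition and intrusions, the shift is +0.04 to +0.16, or 13% to 80% of a true path of -0.2 to -0.3. If the relations run in opposite directions, the shift would instead favour the hypothesis.

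For Hypotheses 1 and 2a the consequence is lost precision only: about 2 to 7 percentage points of power in the linear approximation for r = 0.2 to 0.4, and almost nothing if R² is below about 0.02. The improvement is worth making mainly for 2b.

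**What to change.** - **Hypothesis 2b:** pre-specify post-film distress, post-film attention, sex and film order as covariates in both the mediator and the outcome equation. State the assumption of no unmeasured mediator-outcome confounding, and add a sensitivity analysis showing how strong a remaining confounder would have to be to change the conclusion.
- **Hypothesis 1:** add film order and the two ratings to sex and day.
- **Hypothesis 2a:** add sex, film order and the two ratings to Condition.
- **All three:** report the models without the added covariates as sensitivity analyses.

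No new data are needed. The statistical cost is a few degrees of freedom: in the 2b outcome equation with 114 participants, residual degrees of freedom fall from 114 - 3 = 111 to 114 - 7 = 107 if each covariate is one term. The study is preregistered and recruiting, so the change should be a dated, disclosed update to the preregistration. The article places final analysis after the end of data collection, estimated for July 2026, so the update should be made before that analysis begins.

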### Aims and hypotheses

The overall objective of this project is to examine two mechanisms underlying the relationship between sleep and the development of involuntary intrusive memories, utilizing a well-established experimental analog trauma exposure. The two mechanisms are:

Improved memory consolidation over periods of sleep leads to integration of the trauma memory into the broader memory network, thereby reducing intrusive memories.Sufficient sleep quality/quantity facilitates executive control over spontaneous cognition, including intrusive memories, decreasing the likelihood of their occurrence.

This study will employ a between-subjects design, with two conditions: (1) 2-h daytime nap opportunity, measured using polysomnography; and (2) equal length of controlled waking. Each condition will include *n* = 57 healthy adults, aged 18–49 years old (total *N* = 114, aiming for equal numbers of women and men). OSF preregistration: https://doi.org/10.17605/OSF.IO/MWAHD

Aim 1: Examine the effect of a daytime nap (vs. wake) on intrusive memory frequency.
Hypothesis 1.We will replicate the established finding that a nap, relative to wake, will result in a reduced number of intrusive memories [14, 15] in the 5 days following viewing the trauma film.

Aim 2: Investigate the effect of sleep-related memory consolidation on intrusive memory frequency.
Hypothesis 2a.A nap, relative to wake, will lead to greater recognition memory for the trauma film stimuli immediately after the nap/wake period, as measured by improved recognition of trauma stimuli from the film and reduced endorsement of lure stimuli (film images never seen).
 Hypothesis 2b.Recognition memory for the trauma film immediately after the nap/wake period will mediate the relationship between sleep condition (nap vs wake) and the number of intrusive memories in the following 5 days.

Aim 3: Investigate the effect of overnight sleep on mind wandering and intrusive memory frequency over a 5-day period following analog trauma exposure.
Hypothesis 3a.Reduced quantity of sleep at night will be associated with increased mind wandering and greater frequency of intrusive memories the next day.
 Hypothesis 3b.Mind wandering will mediate the relationship between sleep the previous night and intrusive memories the following day.

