**Figure 1 f1:**
[figure not shown]
Timeline of study participation. During days −7 to −1, participants maintain a regular sleep schedule. Day 0 (lab session) is indicative of a participant with a habitual wake time of 8 am. Lab session timing depends on participant sleep schedule. All sessions are a maximum of 6 h long. For the night following the lab session, participants follow the regular sleep schedule. For the remaining four nights of sleep, participants sleep ad libitum. During days 1–5, participants complete a daily mind wandering task (sustained attention task), fill out a diary for intrusive memories, and repeat the recognition task on the final day.

Phase 2 is the lab session (day 0). Participants wake up 2 h prior to their habitual wake time. This is to ensure sufficient sleep during the nap and to mildly sleep-deprive the wake group. After reporting to the lab in the morning participants are set-up with polysomnography. Following this, they view an analog trauma film in a dark sound attenuated room. Participants are then randomly assigned to one of the two groups: an experimental (nap) group and a controlled (wake) group, for a 2-h period. During this time, those in the wake group can engage in specific activities provided by the researchers including coloring and puzzles. They are unable to use social media, watch videos, view photos, read, or engage in university study/other work during this time. At the end of this experimental period, polysomnography equipment is removed and there is a 30-min delay period for both groups, to allow for the effects of sleep inertia to subside for the nap group. Participants then complete a recognition memory task for images from the trauma film and a sustained attention task to measure mind wandering (hereinafter referred to as “mind wandering task”) in the same sound attenuated room. Following this, participants are provided with instructions for completing an intrusive memory diary.

Phase 3 includes the remaining 5 days of the experiment. Over the next five nights, we will continue to monitor participant sleep with diaries and actigraphy. Participants complete daily intrusive memory diaries, starting as soon as they leave the lab, with six entries at minimum. During each day, they complete the same mind-wandering task completed during the lab session. The recognition task is repeated on day 5. Following study completion, participants attend a debrief meeting.

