#### Recognition and mind wandering tasks

Following the 2-h sleep or wake opportunity, participants complete two tasks. The first is a recognition task. Participants view targets (images from the films) and lures (similar images never seen) and are required to judge whether they witnessed these during the film. The task includes 64 images in total and takes ~10–15 min to complete. Recognition memory task performance will be assessed with the discriminability index (*d-prime* = transformed hits rate − transformed false alarm rate). As a planned secondary analysis, performance on targets, and lures will be individually examined as findings in the literature are inconsistent as to whether performance on targets or lures is driving sleep-related effects on *d-prime* [13, 40].

Mind wandering or off-task thought is related to failures of attention on a range of different sustained attention tasks [64]. The mind wandering task in the current study is an adapted version of a sustained attention to response Go/NoGo task, which has previously been used to elicit and examine mind wandering [65]. Participants are instructed to pay attention to a series of digits and press a button for all digits except the digit 3. The presentation of stimuli is stopped at random times (every 30–70 s) to probe mental state (eg, on/off task) and vigilance of the participants with a series of questions, taking ~18–20 min to complete. The primary outcome from the mind wandering task is frequency of mind wandering.

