##### Post-lab session tasks (days 1–5)

For the 5 days following the lab session, participants complete daily intrusive memory diaries and daily mind-wandering task. Participants are instructed to complete the mind wandering task between the hours of 14:00 and 17:00 each day in a quiet environment. Participants are reminded via text and email each day at 13:55 to complete this task. They are required to complete this task on a computer or laptop with a hard keyboard. The recognition task is repeated once on day 5, with an instruction to complete this in a dark room or after sunset to ensure they can clearly view the images. Participants are instructed to complete the recognition task on a computer screen (rather than a smartphone) and are reminded via text and email on day 5. The links to the recognition task on day 5 and the mind wandering task each day are included in the reminder email. Figure 2 details the schedule of enrolment, study questionnaires, and tasks.

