We will exclude data from the recognition memory task if the participant is not a conscientious responder. This is operationalized as below 50 per cent performance for both targets (images they have seen) and lures (images they have not seen).

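### On the plain reading, day 5 re-shows the day 0 recognition images, so an exploratory day 5 nap-wake difference cannot be attributed to longer-delay consolidation alone

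*Protocol article*

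**What the plan says.** Under Recognition and mind wandering tasks, the protocol article describes a single task: "Participants view targets (images from the films) and lures (similar images never seen". Participants judge whether each image was in the film. On size: "The task includes 64 images in total and takes ~10–15 min to complete". The score is d-prime, defined as "transformed hits rate − transformed false alarm rate".

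Lures are described in similar terms elsewhere. Hypothesis 2a expects "reduced endorsement of lure stimuli (film images never seen", and the Data exclusion section speaks of "lures (images they have not seen".

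On the second administration, Post-lab session tasks states: "The recognition task is repeated once on day 5". The Figure 1 legend agrees that participants "repeat the recognition task on the final day". No parallel form, fresh lure set or split of the 64 images is described.

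Under Analytic strategies, Aim 2, Hypotheses 2a and 2b are to be re-run as exploratory analyses with day 5 recognition replacing day 0 recognition. No adjustment for day 0 is mentioned. The interpretation given is: "This will explore the role of longer-delay memory consolidation on intrusive memory".

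**The concern.** A recognition test is also a learning episode. If the same images are used twice, three things other than memory for the film can shape a day 5 answer:

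- **Repeated answers.** The participant recalls and repeats the day 0 response.
- **Source confusion on lures.** A lure feels familiar because it appeared in the day 0 test.
- **Re-exposure to targets.** A hit on day 5 may owe something to the extra viewing on day 0.

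The design gives this some force. All participants wake 2 h early on day 0, partly so that the wake group is mildly sleep-deprived. That group is then tested without having had a sleep opportunity, while the nap group has had one. A day 0 difference may therefore be partly a temporary difference in alertness. A later test, after intervening nights, could help separate that from lasting memory. Reusing the items weakens the separation, because day 0 answers and day 0 test encoding can differ by arm and persist to day 5.

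What is at stake is the meaning of an exploratory result: a day 5 nap-wake difference could be reported as consolidation at a longer delay when part of it comes from the day 0 test.

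**Working it through.** The plan gives no figure on this point, so there is none to reproduce. The check is a reading of the text plus illustrations under stated assumptions.

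**1. The text side by side.** One image set is described, the task is repeated, and the day 5 score is used instead of the day 0 score. The Discussion lists limitations of the recognition task (variation between people in how distressing the images are, and the less controlled home setting) but does not mention earlier exposure to the images.

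**2. Effect of lure familiarity on the score.** The formula is d-prime = z(hit rate) − z(false alarm rate). Assume a hit rate of 0.80 on day 5 and a false alarm rate of 0.20 before any familiarity effect; neither is in the document.

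| False alarm rate | d-prime |
|---|---|
| 0.20 | 0.842 + 0.842 = 1.68 |
| 0.25 | 0.842 + 0.674 = 1.52 |
| 0.30 | 0.842 + 0.524 = 1.37 |
| 0.40 | 0.842 + 0.253 = 1.10 |

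A rise from 0.20 to 0.30 lowers d-prime by 0.32 with no change in memory for the film. A shift of the same size in both arms produces no arm difference.

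**3. Effect of carry-over on the arm comparison.** Assume a day 0 difference of d = 0.5 (the effect size in the Sample size section), 57 per arm, and no arm difference in anything later. Let a share w of the standardised day 0 difference carry forward, so that day 5 d = w × 0.5. The chance of p < 0.05 in a two-sided two-sample t-test is:

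| w | Day 5 d | Chance of a significant result |
|---|---|---|
| 0 | 0 | 5% |
| 0.25 | 0.125 | 10% |
| 0.50 | 0.25 | 26% |
| 0.75 | 0.375 | 51% |
| 1.00 | 0.50 | 75% |

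Normal check for w = 0.50: 0.25 × √(57/2) = 1.33, and Φ(1.33 − 1.96) is about 0.26.

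**4. Item-level simulation, no lasting arm difference.** Assumptions: 32 targets and 32 lures, mean d-prime 1.5, 57 per arm, and a purely transient day 0 difference of d = 0.35 to 0.60. The plain day 5 d-prime comparison is significant in 6% to 11% of trials when 20% of day 5 answers copy day 0, in 10% to 23% at 40% copying, and in 19% to 49% at 60%. An item-level model that includes the day 0 response to the same image gives 5% to 9%; a separate simulation gave about 7% to 11%. Adjusting for day 0 d-prime instead gives 18% to 66%, with the sign reversed.

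**5. The same model when the nap effect does last.** With a genuine lasting d-prime difference of 0.3 and 40% copying (32 and 32 items, 57 per arm, pooled probit with clustered errors), conditioning on the day 0 response lowers the Condition-by-target coefficient from 0.25 to 0.16 and power from 68% to 43%. At 60% copying, power falls from 73% to 38%. A further simulation gave a fall from about 76–79% to 40–60%. The adjustment limits transient carry-over at the price of removing part of a real effect.

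**The case against.** **Reuse of the images is inferred.** The article says the task is repeated; it does not say that the same 64 images appear. Development of the image set is referred to a supplement that is not shown. This stands, so the point has to be conditional.

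**The question put to participants is about the film.** A reader might infer that the day 5 score is invalid because its lures are no longer unseen. The document does not support that. A lure shown in the day 0 test was still not in the film, so rejecting it remains correct and d-prime remains defined. Earlier exposure adds source errors; it does not make the score meaningless.

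**Lure familiarity is not by itself arm bias.** Both arms take the day 0 test, so a shift common to both cancels in the comparison. Bias needs carry-over of something that differs by arm.

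**The false-positive rates rest on chosen inputs.** They require a transient day 0 difference, no lasting one, and a carry-over share that the document does not supply. At 20% copying the excess is small. If the nap effect lasts, a day 5 difference is largely real.

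**These analyses are labelled exploratory.** This is correct, and it limits the weight of the point. It does not settle what a day 5 difference may be taken to mean.

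**Conclusion.** The point holds as a limit on interpretation. If day 5 uses the day 0 images, a day 5 nap-wake difference cannot be attributed to longer-delay consolidation alone, because the score also reflects the day 0 test. Nothing in the article, including its stated limitations, deals with this.

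A reader might go further and conclude that day 5 d-prime merely carries the day 0 result forward and measures no later retention. That is not supported: the score is confounded but still informative, and the degree of carry-over is unknown. The rates of 10%, 26% and 51% are illustrations for 25%, 50% and 75% carry-over of d = 0.5, not estimates for this trial.

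Only the exploratory day 5 versions of Hypotheses 2a and 2b, and any separate look at targets and lures on day 5, are affected. The main analyses of 2a and 2b use the day 0 test, when the lures are new. This is a minor point and a cheap improvement.

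**What to change.** In Analytic strategies, Aim 2:

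1. State whether day 5 uses the same 64 images. If it does not, say so; the concern then falls away.
2. If it does, replace the reference to consolidation at a longer delay with *recognition at repeat testing*, and state that all day 5 images, lures included, were shown on day 0.
3. Keep the planned day 5 d-prime analyses for 2a and 2b.
4. Add one sensitivity analysis for day 5 Hypothesis 2a: an item-level probit or logistic mixed model of the day 5 response, with target/lure, Condition, their interaction, and the participant's day 0 response to the same image. The term of interest is the Condition-by-target/lure interaction.
5. Report both results. Note that the unadjusted one can include transient day 0 differences, and that the adjusted one conditions on a post-randomisation response and is conservative if the nap effect lasts.

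The item-level model should not replace the planned analysis: it loses power for a lasting effect and yields no participant-level mediator for 2b. Adjusting for day 0 d-prime is not a substitute. The images should not be changed mid-trial, since that would split the day 5 measure.

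The cost is a more modest exploratory claim and one extra model on responses that the two test sessions already produce.
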